# Study protocol for a randomized controlled trial to test for preventive effects of diabetic foot ulceration by telemedicine that includes sensor-equipped insoles combined with photo documentation

**DOI:** 10.1186/s13063-019-3623-x

**Published:** 2019-08-22

**Keywords:** Diabetic foot syndrome, Prevention of DFUs, Temperature measurement, Smartphone application, Sensor-equipped insole

## Abstract

**Background:**

Early detection of diabetic foot ulcerations (DFUs) can avoid or delay any progression into more severe stages, which may require limb amputation or lead to infectious sequelae and death. However, frequent clinical screening would be too intrusive and costly, and self-examination may be hampered by concomitant diseases and social disabilities. In addition, it requires professional knowledge and experience using specialized devices. Researchers reported that skin temperature monitoring could reduce the risk of DFUs in high-risk patients. The main research objects in this field are effective and convenient means of temperature measurement, accurate and reasonable early warning mechanisms, and timely and appropriate interventions. This trial aims to investigate the effectiveness of daily home-based foot temperature measurements in the prevention of DFUs with the aid of intelligent sensor-equipped insoles combined with photo documentation.

**Methods/Design:**

In this open-label, prospective, randomized, 24-month trial, 300 patients with diabetes mellitus (type 1 or 2) and severe diabetic peripheral neuropathy (vibration sensation ≤ 4/8), aged 18–85 years, will be recruited and assigned to control and intervention groups in a ratio of 1:1. Main inclusion criteria to be eligible for study participation encompass in particular risk group 2 or 3 for the development of DFUs using the diabetic foot risk classification system (as specified by the International Working Group on the Diabetic Feet [IWGDF]) and the ability to use a mobile phone.

**Interventions:**

Participants in both groups will receive education about regular foot care at the beginning of the study (visit 0). In the intervention group, every patient will receive a pair of slippers with the inserted sensor-equipped insole as well as a smartphone with the corresponding smartphone application (Smart Prevent Diabetic Feet Application). The insole is a tool that records the temperature variabilities of the plantar foot. Patients will measure their foot temperature twice a day at home with a time interval > 4 h during the entire course of the study (24 months). The measured data will be initially analyzed and visualized, and further transferred to a remote server that allows the physician to perform specific interpretations. In case of temperature differences > 1.5 °C between left and right corresponding sites lasting > 32 h (assigned alarm level 4), the physician will start an intervention phase, which requires the patient to reduce daily activities and relax his feet for five days. At the same time, photo documentation is encouraged to be performed by the patient. Possibly, additional visits to a private doctor or clinical examinations will be arranged for the patient during this intervention period. Outcomes: The primary outcome is foot ulceration, evaluated by a physician, and occurring at any point during the study.

**Discussion:**

This study addresses principal aspects in the prevention of DFUs. First, the sensor-equipped insole will be evaluated for daily performance in home-based measurements of foot temperatures. Second, a telemedicine structure is tested that evaluates sensor data automatically and proposes suitable intervention measures under the supervision of a physician. Third, predictive models for DFUs will be built using the collected sensor data allowing for interpretations, which in the future may support medical care providers.

**Trial registration:**

German Clinical Trials Register (DRKS), DRKS00013798. Registered on 18 January 2018.

**Electronic supplementary material:**

The online version of this article (10.1186/s13063-019-3623-x) contains supplementary material, which is available to authorized users.

## Background

According to the definition of the World Health Organization (WHO), diabetic foot syndrome (DFS) encompasses all foot complications, constituting an “ulceration of the foot (distally from the ankle and including the ankle) associated with neuropathy and different grades of ischemia and infection” [1]. It increases the risk of limb amputation, and even mortality, if left untreated [2]. In Germany, about 40,000 legs, feet, or toes are amputated, with 70% of major amputations and 85% of minor amputations due to DFS. In addition, foot lesions in diabetic patients impose an enormous social and economic burden across the world. In the US, Rogers et al. reported that $18 billion were spent on the care of diabetic foot ulcers (DFUs) and $11.7 billion sum up as consequences of lower extremity amputations [3].

Among the reasons for DFS, diabetic foot neuropathy is the major contributing factor for foot complications (50% as a single cause, 30–50% as a cause in combination with angiopathy [4]), because it affects the ability of the foot to feel and sense [5–7]. This is why patients with diabetic neuropathy are not able to realize injuries to their feet. Most of the complications develop due to infection and ulceration in the foot [8, 9]. The early signs of DFS include fissures, blisters, abundant callus formation, redness, and increased temperature [10]. A physician may diagnose the exact cause by analyzing these physical features [11].

It is possible to delay or even avoid the development of DFUs with adequate treatment at early stages. Usually, clinicians assess the general condition through analyzing ankle brachial pressure indices, plantar pressure profiles, and testing for foot neuropathy [12]. Additionally, advanced technologies like corneal confocal microscopy, magnetic resonance tomography, and Doppler ultrasonography provide tools to diagnose the prevalence of peripheral neuropathy and angiopathy, foot ulcers, and its risks [13]. However, these methods are considered intrusive and are costly; patient compliance is lacking, especially with frequent doctor’s visits [2]. On the other hand, patient self-assessment has limitations such as lack of knowledge about this condition, difficulties using specialized equipment, and impaired physical mobility. More effective and advanced approaches need to be investigated to provide flexible and comprehensive foot care for patients at risk for the DFS.

Elevated plantar temperatures have been reported to be an early sign of incipient DFUs. In the studies of Lavery et al. and Armstrong et al., home temperature monitoring and reduced activities have been verified to be effective to reduce the incidence of DFUs in high-risk patients [14, 15]. In the study of Lazo-Porras et al., the effectiveness of foot thermometry (TempStat™ for thermal image capture) to prevent DFUs was investigated, together with mHealth reminders (SMS and voice messaging), in an evaluator-blinded randomized 12-month trial. The authors highlighted the importance to evaluate adherence to daily home-based measurements [16]. Furthermore, a left-to-right foot temperature difference of > 2.2 °C as a proposed threshold for an impending ulceration has been investigated comprehensively by Wijlens et al. in 20 patients with diabetes and peripheral neuropathy. Their conclusion was that the > 2.2 °C threshold is only acceptable if it is confirmed after 24 h in a repeated measure and if, in addition, the temperature difference is individually corrected depending on baseline measurements [17]. In addition to neuropathic ulcers [18, 19], one has to consider osteomyelitis [20, 21] and the disease termed Charcot foot [22] as differential diagnoses in the case of elevated plantar temperatures.

On the other hand, decreased foot temperatures may point to a vascular insufficiency in the foot [23]. Therefore, foot temperature monitoring with thermometers, thermal imaging techniques, wearable temperature techniques (socks, insoles, and shoes) has been widely tested to date. For example, Netten et al. explored the temperature discrimination thresholds between “no,” “local,” or “diffuse” DFUs with a high-resolution infrared thermal imaging technique [24]. Fraiwan et al. implemented a mobile thermal imaging system with an automated method to identify possible ulcers in diabetic patients [11]. These pioneering works may open a window for patients to check for their foot condition in a feasible and comfortable fashion in the future.

Moreover, in the study by Fryberg et al., a novel smart mat technology was evaluated for predicting impending DFUs in a 34-week cohort study that enrolled 132 patients with diabetes. Their results support the notion that the remote temperature-monitoring system could be a feasible and efficient strategy to early identify DFUs, but the asymmetry thresholds have a significant influence on the sensitivity and specificity. Comparing the 2.22 °C and 3.20 °C thresholds, sensitivity decreased from 97% to 70%, but the specificity increased from 43% to 68% [25]. Therefore, effective and convenient means of temperature measurements such as home-based wearable technologies, accurate and reasonable early warning mechanisms with disparate asymmetry thresholds, followed by timely and appropriate interventions are the main research focus in this field.

From our perspective, home-based monitoring of plantar foot temperatures may be regarded as an effective method in the early detection and possible prevention of DFUs. In this study, by utilizing a novel sensor-equipped insole, we aim to establish a telemedicine structure with a remote server and the corresponding smartphone app to timely monitor changes of plantar foot temperatures in diabetes patients. The evidence obtained will include a set-up with predefined standardized temperature recordings and a telemedicine aspect allowing for feedback and alarming as well as picture recordings. The outcome of our study will ultimately allow us to determine if and to which extent such an effort may reduce the number of diabetic foot ulcerations and other medical foot conditions in such a cohort.

## Methods/Design

### Objectives

The present study aims to investigate the hypothesis that a twice-daily recording of foot temperatures with the aid of the sensor-equipped insole (Medixfeet Insole®, Thorsis Technologies GmbH) can reduce the risk of ulcer formation.

### Primary specific aim

The primary objective of the present study was to compare the incidence of DFUs during the study period between patients who only receive education about regular foot care and those patients who additionally proceed with daily measurements of foot temperatures with the sensor-equipped insole, together with an app-based warning system and self-imaging of feet for incipient ulcer development.

### Secondary specific aims

The secondary objectives of the present study were to:
collect safety-relevant information concerning the equipment (insole)
frequency of adverse events (AEs)frequency of serious adverse events (SAEs)quantify precursors of the primary endpoint
redness in the foot areainfections in the foot areawounds in the foot areaevaluate the changes of quality of life independent of primary and secondary endpointsassess the adherence to daily two-time temperature measurements based on data acquisition by the apprecord the alarm frequency in the intervention group based on data collected by the appdetect “slow” temperature drops as an indicator of circulatory disordersassess the adherence to photo documentation

### Study design

This open-label trial will randomize 300 high-risk patients with diabetes and advanced polyneuropathy, that lack severe peripheral angiopathy, into two groups with a 1:1 ratio.

At the screening visit, all potential study participants will first be informed about the aim and purpose of the study. They will be interviewed for past medical foot problems with documentation thereof and will thereafter be examined for polyneuropathy and blood circulation disorders (see below). Regarding the study-specific inclusion and exclusion criteria (compare Fig. 1), the study physician informs the patient about their possible suitability for participation and the modalities of the study. If patients are eligible for the protocol, they will be enrolled only after giving informed consent (see Additional file 1).

**Fig. 1 Fig1:**
[figure not shown]
Algorithm for possible study enrollment, with description of the inclusion, exclusion and termination criteria of the study in the screening process

In a next step, patients will be randomized into control or intervention group in a ratio of 1:1. Two weeks later, at visit 0, they will be trained by a qualified study physician about regular foot care measures to prevent foot ulcers (standardized patient education) (see Additional file 2). The non-intervention group will not undergo any further immediate intervention; however, research participants in this group will be seen at regular follow-up visits at six-month intervals (Fig. 2). In the intervention group, every patient receives a pair of slippers with inserted sensor-equipped insoles as well as a smartphone with a Smart Prevent Diabetic Feet Application (SPDFA) (Fig. 3, see Additional file 3). They will perform measurements of their foot temperatures twice a day at home, with time intervals > 4 h during the entire study course, which comprises 24 months. In case of temperature differences > 1.5 °C between left and right corresponding sensor sites, and lasting > 32 h, the study participant will be instructed to reduce daily activities and relax his feet for five days. Additionally, the participant will receive a notification by the app to take pictures with his smartphone from the dorsal and (possibly with help of care providers) plantar feet that are transferred to the study center. In the app, essential guidance and foot masks help the patient to capture standardized foot images (Fig. 5). Depending on the findings of the photo documentation, additional visits to the study center to perform clinical examinations will be arranged for the patient during this intervention period.

**Fig. 2 Fig2:**
[figure not shown]
**a*** Flow diagram* of the study showing procedures, activities, and processes. **b*** Figure* showing the Standard Protocol Items: Recommendations for Interventional Trials (SPIRIT see Additional file 4) for this study

**Fig. 3 Fig3:**
[figure not shown]
Study materials for patients in the intervention group showing the sensor-equipped insole (Medixfeet Insole®, Thorsis Technologies GmbH) and the Smart Prevent Diabetic Feet Application (SPDFA)

In addition, patients in both groups are required to consult a physician when early signs of foot ulceration are noted by self-inspection of the feet (e.g. redness, pain, sores). Follow-up visits are carried out after enrollment in the study at months 6, 12, 18, and 24 by a registered nurse and a physician trained to diagnose and treat DFS. Visits 1 and 3 (after 6 and 18 months, respectively) encompass the evaluation of patient’s foot status, control of unexpected events, summary of endpoints, and assessment of the collected sensor data. Visits 2 and 4 (after 12 and 24 months, respectively) additionally include the assessment of outcome measures, patient’s wellbeing evaluation by WHO-5-questionaire, as well as taking pictures with normal illumination and infrared light from the patient’s feet (Fig. 2).

The primary endpoint of the study is DFU formation (more precisely, the time until ulcers form) and the total number of ulcerations in each group. Secondary endpoints will include evaluation of AEs and SAEs, precursors of the primary endpoint as listed above, assessment of quality of life using an interactive patient’s diary (Fig. 6), patient compliance, information about temperature alarms—including “slow” temperature drops, and acquisition of photo documentation.

If a foot ulcer occurs in a patient, it will be treated according to the usual measures of standard clinical care. Possible discontinuation of the study occurs according to the defined termination criteria (Fig. 1).

The SPDFA receives the measured data of the sensor-equipped insole via low-energy Bluetooth® connectivity. It then performs an initial analysis of temperature differences and visualizes these. Thereafter, the temperature recordings are transferred from the SPDFA to a study server. This server is located in the premises of the computer center of the Medical Faculty of the Otto-von-Guericke University Magdeburg. The data may be exported from the study server in a suitable format (SAS / SPSS) for statistical analysis at the Institute of Biometry and Medical Informatics. The final report will be compiled no later than one year after the end of the study.

### Participant recruitment and selection criteria

Recruitment is carried out by practicing diabetologists and podiatrists in the Polyclinic of the University Hospital Magdeburg. The study will enroll 300 patients aged 18–85 years with type 1 or type 2 diabetes mellitus and exhibiting severe diabetic peripheral neuropathy (vibration sensation ≤ 4/8) with or without a history of ulceration. They will be eligible only when they are classified as high-risk patients, i.e. risk class 2 or 3 as defined by the diabetic foot risk classification system (as specified by the IWGDF) [26, 27]. It is based on a short questionnaire about previous history of ulceration and/or partial foot amputation, foot evaluation to detect bunion, rigid deformities (such as hammer digit or claw toe), and prominent metatarsal heads, as well as neuropathy testing using the vibration perception threshold and the Semmes-Weinstein monofilament [28]. The participants of the study have to be able to use a smartphone and its applications. The study excludes patients with active ulcer, arthropathy, tumor disease, as well as those with foot infection, macroangiopathy of the lower extremities (ABI < 0.5), heart failure classes III/IV according to NYHA, physical deformities (amputations, foot, leg, spinal deformities affecting the gait), visual impairment that limits normal use of smartphones, myocardial infarction within 12 weeks before study protocol inclusion, or pregnancy. The principal investigator has the right to preclude participation due to any reason in his personal opinion and in accordance with the inclusion and exclusion criteria as summarized (Fig. 1).

### Baseline data collection

At the screening visit, the study physicians record the past medical history by means of a foot documentation sheet recommended by the Foot Working Group of the German Diabetes Society. It includes the following items:
Previous foot lesions, deformities, and surgeriesDetails about the previous shoe supplyPresence of blood supply disorders (ischemia and PAD)Burning, numbness, weakness, cramps or pain in the legs and feet

In addition to the interview, a series of tests are carried out to determine the degree of polyneuropathy and blood supply disorders:
Monofilament test to check the sensation of touch and pressureTip-Therm Test to check the temperature sensationTuning fork test for measuring depth sensitivity and vibration sensationTesting the sensation of pain with a disposable needleDoppler ultrasound test for the measurement of circulatory disordersMuscle self-reflex statusBlood pressure measurement (for ABI)

If patients are eligible for the protocol, the study physician obtains informed consent at screening visit through a written consent form with the signature of the potential trial participant.

### Randomization

In the University Clinic for Nephrology and Hypertension, Diabetes and Endocrinology, randomization is performed using the software RITA (from Statsol, Lübeck). Three hundred patients will be assigned to two groups with a 1:1 ratio based on a stratification according to the prevalent risk group (2 or 3), gender, age (< 60 years vs ≥ 60 years), and the degree of neuropathy (restriction of vibration sensation, using the minimization algorithm of Pocock and Simon [29]). Randomization to the study protocol will be based on the intention-to-treat principle. The randomization is not concealed to the physicians and to the study population at any time after informed written consent of the patients.

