## Trial status

This manuscript is based on version 1.6 of the trial protocol, dated 18 February 2019. Recruitment for this study began on 30 January 2018 and should be completed by 30 December 2019.

At the time of submission, our study has already recruited 196 patients; 87 patients were randomized into the intervention group. Of the 87 patients, 72 are active by daily measurements of foot temperatures with our system. The study is widely known in the area of Saxony-Anhalt; currently, a growing number of people with diabetes are eager to participate in the trial.

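### As worded, the protocol lifts concealment at consent, which comes before randomisation, so nothing stated protects the allocation up to the moment of assignment

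*Protocol article*

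**What the plan says.** All references are to the protocol article.

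- **Concealment (Randomization):** "The randomization is not concealed to the physicians and to the study population at any time after informed written consent of the patients".
- **Order of steps (Study design):** after eligibility is checked, "they will be enrolled only after giving informed consent". Then: "In a next step, patients will be randomized into control or intervention group in a ratio of 1:1". After that: "Two weeks later, at visit 0, they will be trained". Baseline data collection also places written consent at the screening visit.
- **Blinding (Study design):** "This open-label trial will randomize 300 high-risk patients with diabetes".
- **Method (Randomization):** "Three hundred patients will be assigned to two groups with a 1:1 ratio", by Pocock-Simon minimisation on risk group, gender, age and degree of neuropathy. It is run with randomisation software in the study clinic. The article does not give the assignment probability.
- **Recruitment and preclusion (Participant recruitment and selection criteria):** one polyclinic is named. "The principal investigator has the right to preclude participation due to any reason in his personal opinion"; the sentence goes on to tie this right to the eligibility criteria as well.
- **Accrual (Trial status):** "our study has already recruited 196 patients; 87 patients were randomized into the intervention group". Neither the number of controls nor the total randomised is given.

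**The concern.** Allocation concealment and blinding are different safeguards. An open-label trial cannot keep the arm secret after assignment, but it can and should keep it secret until then. The Randomization section sets the point of openness at consent, one step too early.

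The setting makes the gap matter. In one clinic with open treatment, staff know who went where. Minimisation is driven by the factor totals of earlier patients, so someone who tracks them can often see which arm the next patient is likely to receive. If a patient can still be precluded at that point, even partly on opinion, knowledge of the likely arm can influence who enters. The Cox model adjusts for age, gender, risk class and neuropathy. It cannot adjust for what a clinician sees but the data do not record, such as expected adherence or frailty.

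**Working it through.** **1. Order of events.** Set side by side, the sections give this sequence:

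| Step | Event | Section |
|---|---|---|
| 1 | Screening and eligibility check | Study design |
| 2 | Written consent | Study design; Baseline data collection |
| 3 | Concealment ends, as worded | Randomization |
| 4 | Assignment by minimisation | Study design; Randomization |
| 5 | Visit 0, two weeks after assignment | Study design |

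Step 3 precedes step 4. Nothing in the article says the assignment is hidden between steps 2 and 4, or that preclusion must be settled before step 4.

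**2. How predictable the next arm could be.** The article does not give the settings, so these are assumptions: 196 patients, equal factor weights, three binary factors, and neuropathy with three or five levels. In simulation, minimisation preferred one arm in about 80% to 82% of assignments and was tied in the rest. Someone who tracks the totals and guesses the preferred arm is right with probability

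f × p + (1 − f) × 0.5,

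where f is the share of assignments with a preferred arm and p is the probability of assigning it.

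- p = 1.0: 0.80 × 1.0 + 0.20 × 0.5 = 0.90
- p = 0.8: 0.82 × 0.8 + 0.18 × 0.5 = 0.75
- p = 0.6: 0.81 × 0.6 + 0.19 × 0.5 = 0.58

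A fully concealed coin toss gives 0.50. These figures show what could be foreseen. They do not show that anyone did so.

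**3. Accrual figures (conditional).** The stated figure is 87 of 196, or 44.4%. If all 196 had been randomised, controls = 196 − 87 = 109, the gap is 109 − 87 = 22, and the expected split is 98:98.

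- Simple 1:1 randomisation: P(X ≤ 87) for a binomial (196, 0.5) is 0.067, two-sided 0.13. This is unremarkable.
- Minimisation, 8,000 simulated runs per setting, with five neuropathy levels and an assumed factor mix:

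| Assignment probability | Range of intervention-arm size | P(X ≤ 87) |
|---|---|---|
| 1.0 | 97–100 | 0 of 8,000 |
| 0.8 | 94–102 | 0 of 8,000 |
| 2/3 | 91–106 | 0 of 8,000 |
| 0.6 | 85–112 | about 0.0003 |
| 0.55 | 78–115 | about 0.007 |

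If 22 recruits were awaiting randomisation, 196 − 22 = 174 were randomised, the split is 87:87, and nothing is discrepant. Fewer would do if a small imbalance is allowed.

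Is 22 plausible? Recruitment began on 30 January 2018. Assume submission fell between the protocol version date (18 February 2019) and publication (22 August 2019), that is 12.6 to 18.7 months. Accrual was then 196/12.6 ≈ 15.5 to 196/18.7 ≈ 10.5 per month, so 22 patients is about 1.4 to 2.1 months of recruitment. That is long for the step after consent, but it cannot be excluded.

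**The case against.** The strongest reply is that the sentence only means open-label: patients and physicians are not blinded once in the study. Eligibility is assessed before consent, minimisation needs no pre-generated list that could be read in advance, and no section says an upcoming assignment is disclosed. This is a fair reading and may be what was meant. But Study design already declares the trial open-label, so the sentence adds something about randomisation itself, and what it adds puts openness before assignment.

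Four further objections stand, and they limit the point:

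- A reader might infer that the investigator holds an unlimited veto. The same sentence refers to the inclusion and exclusion criteria, and nothing says the right is used once the arm is known. What can be said is that personal opinion is one ground and that no cut-off before allocation is stated.
- A reader might infer that the minimisation is deterministic. The article does not say so, and the full protocol may well specify a random element.
- A reader might infer from 87 of 196 that the procedure failed or was manipulated. Recruited is not the same as randomised, and the control count is missing. Moreover, steering who enters changes the make-up of the arms while minimisation still equalises their sizes, so a gap in numbers is not a sign of selection bias.
- Analysis of every randomised patient is already provided for by intention-to-treat, so nothing needs adding there.

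**Conclusion.** The point holds as a defect in a stated rule. The Randomization section ties the end of concealment to consent, consent precedes assignment, and no other section of the article protects the assignment. The risk is selection bias in a one-clinic, open-label trial with minimisation. The size of any bias cannot be computed from the document. The predictability figures (0.58 to 0.90 correct guesses for assignment probabilities from 0.6 to 1.0) rest on assumed settings and on someone tracking the totals.

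The accrual point is secondary and conditional. An 87:109 split would be very unlikely under minimisation with an assignment probability of about 0.6 or more, but only if all 196 recruits had been randomised, which the article does not state. It calls for the missing count and does not support any conclusion that allocation was subverted.

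**What to change.** 1. Reword the Randomization section along these lines: *Consent, eligibility and any decision by the investigator to preclude a patient are recorded and locked in the randomisation system before the allocation is generated. The allocation is concealed from all staff and patients until that moment and is open only afterwards. No patient may be precluded once the allocation is known.*
2. Confirm that the minimisation includes a random element. If the full protocol already specifies one, nothing changes.
3. In Trial status, give the number randomised to each arm and the number recruited but not yet randomised.

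The cost is a few sentences, possibly one software setting, and a count from the allocation log. If a random element has to be added, balance on the four factors becomes slightly looser. Under the simulation settings above, the 99th percentile of the gap between arms at 196 patients is 4 with probability 0.8, against 2 with a deterministic rule.
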